## APPENDIX 6 - Protocol for IPCARD-SPN

### BACKGROUND:

In the UK approximately 86% of those with LC are diagnosed at a stage when curative treatment is not possible and less than 25% survive one year following diagnosis [1-3]. Lung cancer is diagnosed at a later stage in the UK and survival rates are lower than in most other Western European countries [1, 3, 4]. Attempts to address late LC diagnosis in the UK have included the National Institute of Clinical Excellence (NICE) recommendation that urgent CXR is offered to patients presenting with any 1 of 10 specified symptoms [5]. However, the report acknowledges the lack of evidence about the predictive value of these symptoms and therefore the weak evidence base upon which these guidelines rest.

Recent research has strengthened evidence that LC can be symptomatic even years prior to diagnosis [6-8]. However, these studies do not provide strong evidence of the diagnostic value of early symptoms. Findings of a primary care based case-control study suggest that those with LC report symptoms to their GP more frequently than randomly selected controls even 6-24 months prior to diagnosis. However the applicability of the PPVs reported for symptoms, is limited by the possibility of recording biases in GP records. Furthermore, recent research has indicated that many lung cancer symptoms are unrecognised and not reported to GPs [8].

Predictive values of symptoms for lung cancer diagnosis obtained from previous research [4, 5] and clinical decision support aids based upon these datasets (e.g. RATS [10]), do not distinguish between early and late stage lung cancer. Existing datasets based upon GP paper records do not provide the power to identify symptoms of early stage disease, and risk scores based upon these datasets assume no difference between symptoms of early and late stage LC. Electronic General Practice Research Database (GPRD) datasets, although providing greater power, do not provide detailed information about symptom experiences or record multiple symptoms with accuracy, information which is likely to be necessary to identify symptoms which predict early stage LC. The SPUtNik study provides a unique opportunity to ascertain whether or not it is possible to distinguish between malignant and non-malignant solitary nodules on the basis of symptoms. The collection of symptom data within SPUtNik will allow the identification of symptoms associated with early malignant disease. Apparent associations of symptoms with LC diagnosis in previous research might be explained by confounding; symptoms might be predictive of chronic respiratory disease or lung lesions more generally. The inclusion of symptom data within the SPUtNik Trial would also enable the identification of symptoms which, when incorporated into a diagnostic algorithm might improve the diagnostic performance of FDG-PET and DCE-CT scans. The IPCARD-SPN study will use the IPCARD symptoms risks, and co-morbidities questionnaire within a prospective study design to identify symptoms which distinguish between malignant and non-malignant solitary nodules.

### IPCARD DEVELOPMENT

Qualitative research with those with lung cancer and early stage LC (RCUK fellowship) identified lay descriptions of symptom experiences in these groups [7]. These lay descriptors were incorporated into a symptom, risk and co-morbidities questionnaire which was developed with newly diagnosed LC patients (RCUK fellowship - [name]). The questionnaire is designed to elicit information about symptom experiences or changes in health status that might have the potential to distinguish between those with LC and non-malignant disease that commonly occurs in those with a smoking history. The questionnaire contains:

- Items identified in the International Primary Care Respiratory Group guidelines designed to identify Chronic Obstructive Pulmonary Disease (COPD) and to distinguish between COPD and asthma [11].
- Lay descriptors of breathlessness identified in studies with patients with asthma, COPD, interstitial lung disease, cardiac failure and lung cancer [12].
- A component developed with LC patients that uses lay descriptors and open questions to record symptoms and changes in health in ten areas: cough, chest/shoulder pain, breathing, skin condition,

joint or bone aches, digestive and bowel changes, weight loss, haemoptysis, voice changes, hoarseness and any other changes in health in the previous two years.

- Risk information including smoking history, family history, known occupational exposures and more recently identified risk factors - previous diagnosis of pneumonia or malignancy [13]
- Co-morbidities.

The questionnaire has been validated with a CXR population (NIHR funded IPCARD Feasibility Study: co-lead by [name] and [name]). This has enabled the addition of descriptors of symptoms of non-malignant chest and respiratory disease which might have discriminatory value for LC. Participants with early stage LC, late stage LC, COPD, asthma and heart disease have been purposively sampled within qualitative research to ensure that IPCARD adequately records the symptom experiences of these groups. Cognitive and semi-structured interviews have been used to establish the content validity of the questionnaire and the high quality of the symptom data obtained. Test-retest reliability will be evaluated by September 2012. In CXR populations refusal rates have been low (approximately 5%) and data completion high (>80%). Most non-response is accounted for by participants taking partially completed questionnaires away from the clinical site and not returning them by post. The average response rate for the two centres that have now completed their second episode of recruitment is >70%.

#### **AIMS:**

- To identify the PPV and NPV of symptoms that distinguish between malignant and non-malignant solitary pulmonary nodules
- To ascertain whether or not the inclusion of symptoms found to distinguish between malignant and non-malignant nodules increases the diagnostic value of DCE-CT and FDG-PET.

#### **SAMPLE SIZE**

Sample size calculations for the analyses (assuming a two sided 5% alpha) using 257 cases of lung cancer and 118 without LC, gave 80% power to detect a difference in a rare or low frequency variable of 10% (from 5% in non-LC to 15% in LC) or 80% power to detect a difference in a more common variable of 14% (from 16% in non-LC to 30% in LC or from 22% in non-LC to 36% in LC). For a more prevalent LC symptom, 257 cases of lung cancer and 118 without LC gave 80% power to detect a difference of 16% (from 34% in non-LC to 50% in LC). The SPUtNik Trial, which anticipates identifying 257 cases of LC and 118 non-malignant lesions, is adequately powered to detect odds ratios for all symptoms (except rare symptoms) likely to have diagnostic value (>2 or <0.5) in clinical populations.

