#### Sample size consideration for each test separately

Published sensitivity for F-DG-PET for the characterisation of SPN vary between 77 and 96% (pooled weighted average: 92%) and specificity varies between 76 and 100% (pooled weighted average: 90%). Published sensitivity and specificity values for DCE-CT vary between 81 and 100% (pooled weighted average: 87%) and 29 and 100% (pooled weighted average: 83%) respectively. Based on two previous UK studies, the mean prevalence of malignancy in indeterminate SPN has been reported as 68.5% [18]. At this prevalence, a sample size of 375 will produce approximately 257 malignant and 118 benign SPNs. This will give confidence limits for sensitivity and specificity of DCE-CT of 87% +/- 4.1% and 83% +/- 6.8% respectively, with sensitivity and specificity values for F-DG-PET of 92% +/- 3.3% and 90% +/- 5.4% respectively. These estimates will provide sufficiently narrow confidence limits to allow precise economic modelling based on the results. For the purposes of economic analyses, we will also consider combining our data with the meta-analysis results from our systematic review (section 8.2), where previous studies we currently know about total 217 patients who had undergone both techniques [8-10]. Recruitment rates are anticipated to be high (70%) because DCE-CT will be additional rather than an alternative to normal care, and is readily incorporated into the existing PET-CT examination. We expect to recruit the required sample size (375) in 18 months. With a 70% recruitment percentage of all meeting the inclusion criteria, in order to recruit 375 patients we need to invite  $375/0.7 = 536$  patients.

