### Statistical analysis

#### (i) Diagnostic accuracy for 2 year follow-up

We will consider the diagnostic accuracy of positive FDG-PET and DCE-CT, both separately and in conjunction, in relation to a diagnosis of lung cancer by 2 years. In these analyses we will only be able to use those patients for whom the presence of lung cancer by 2 years is known; i.e. those without diagnosed lung cancer who drop-out before the end of 2 years will be excluded. This is likely to be small.

Initially, the separate diagnostic performance of FDG-PET/CT and DCE-CT will be examined using diagnostic criteria defined and over the full range of possible threshold values. At each threshold sensitivity and specificity will be estimated (with 95% confidence intervals), and the Receiver Operator Characteristic (ROC) curve will be calculated. The optimal cut-point from the range of values will be reported based on keeping the sensitivity above 90% and maximising specificity within this limitation. An alternative cut-point that provides the best trade off in sensitivity and specificity will also be reported. The sensitivity, specificity, positive predictive value (PPV) and negative predictive value (NPV) at these cut-points will then be presented with 95% confidence intervals. When translating sensitivity and specificity to PPV and NPV, we will need to assume a particular prevalence. This will be based on the prevalence in our study, and also we will report PPV and NPV for a range of other prevalence's reported in the literature (identified from our systematic review).

Secondly, the diagnostic performance of FDG-PET/CT and DCE-CT combined will also be examined using the same techniques as above; we will class patients as 'positive' if they have both FDG-PET and DCE-CT positive, and all others as 'negative'. Again, a range of different thresholds for both FDG and DCE will be considered.

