#### **RECRUITMENT STRATEGY AND CONSENT**

Potential SPUtNik participants will be introduced to the IPCARD-SPN study by the research nurse or PET coordinator either by phone or in clinic. They will be given the IPCARD-SPN questionnaire along with the SPUtNik patient information sheet, which contains a section about the IPCARD-SPN study.

The questionnaire contains no identifiable patient information. Patients may fill in the questionnaire prior to attending the scan appointments and bring it along to the scan appointment. At the scan appointment the research nurse or radiographer will take consent for the SPUtNik study, which includes an optional part for the IPCARD-SPN trial. If the patient consents to the IPCARD-SPN trial, the SPUtNik trial code will be added to the front of the questionnaire and completed questionnaires can be left with the research nurse. For incomplete questionnaires the SPUtNik code will be added and the patient given a Free-Post return envelope and asked to return the questionnaire by post within 2 days.

Participants will be told that they may withdraw consent at any time by telephoning the local hospital site a number is given on the patient information sheet.

Date received will be recorded for returned questionnaires and they will be prepared for automated data entry. Diagnosis will be obtained two years following recruitment from SPUtNik Trial data.

A second copy of the IPCARD questionnaire will be posted to all patients who have not received a lung cancer diagnosis after 1 year (12-18 months) of follow up. This copy will contain the SPUtNik code and be clearly marked IPCARD2. It will be posted with a cover letter explaining why the patient has been asked to complete the questionnaire for a second time and a prepaid envelope to return the questionnaire to SCTU.

Research staff, are instructed to ensure questionnaires are not sent to patients that have already received a diagnosis of lung cancer, are terminally ill or have died.

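### IPCARD-SPN power counts all 375 patients although participation is optional, and the odds-ratio claim is too broad even at full response

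*Protocol*

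**What the plan says.** Appendix 6, Sample Size, "assuming a two sided 5% alpha", gives its power "using 257 cases of lung cancer and 118 without LC, gave 80% power" for four contrasts in symptom frequency (non-LC against LC):

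- 5% v 15%, described as rare or low frequency;
- 16% v 30% and 22% v 36%, both described as more common;
- 34% v 50%, described as more prevalent.

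The counts come from the main trial. Section 9.1 says that "a sample size of 375 will produce approximately 257 malignant and 118 benign SPNs". Section 7 ends recruitment once 375 patients have been recruited and have had a DCE-CT scan.

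The same appendix then claims that the trial "is adequately powered to detect odds ratios for all symptoms (except rare symptoms) likely to have diagnostic value (>2 or <0.5").

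On participation, Appendix 6 describes a consent form "which includes an optional part for the IPCARD-SPN trial" and allows incomplete questionnaires to be posted back. On experience so far, IPCARD Development reports about 5% refusal and more than 80% data completion in chest X-ray populations, and adds: "The average response rate for the two centres that have now completed their second episode of recruitment is >70" per cent. It puts most non-response down to part-completed forms that were taken away and never returned.

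**The concern.** The power statement treats every trial patient as a questionnaire respondent. The appendix itself says that participation is optional and that response fell short of complete in its own earlier work. Section 9.1 divides by 0.7 to allow for uptake of the main trial (375/0.7 = 536 invitations), but nothing comparable is done for the questionnaire.

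The odds-ratio sentence raises a second problem that needs no assumption about response. It extends four specific contrasts, all with the symptom more frequent in lung cancer, to every non-rare symptom and to both directions of association.

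This affects the sub-study's result. Under the modelling strategy in Appendix 6, only symptoms with a univariate p below 0.05 enter the stepwise model, and the symptom score is built from those that survive. Low power therefore removes real symptoms from the score, while the text assures the reader that power was adequate.

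**Working it through.** **Inputs.** Two-sided alpha 0.05, 257 LC and 118 non-LC, and the four contrasts (Appendix 6, Sample Size). The counts are 375 × 0.685 ≈ 257 and 375 − 257 = 118 (Section 9.1). The response rates are assumptions. Appendix 6 gives only a lower bound (above 70%) and about 5% refusal, so a range from 70% to 100% is shown.

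**Formula.** Pooled two-proportion normal test. With non-LC proportion p1 and size n1, LC proportion p2 and size n2, and p̄ = (n1p1 + n2p2)/(n1 + n2):

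- s0 = √[p̄(1 − p̄)(1/n1 + 1/n2)]
- s1 = √[p1(1 − p1)/n1 + p2(1 − p2)/n2]
- power = Φ[(|p2 − p1| − 1.96·s0)/s1]

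**Step 1: reproduce the stated 80%.** For 16% v 30% at 118/257: p̄ = 0.256, s0 = 0.0485, s1 = 0.0442, and (0.14 − 1.96 × 0.0485)/0.0442 ≈ 1.015, so power is 84.5%. The four contrasts give 83.8%, 84.5%, 78.7% and 83.2%. With a continuity correction they give 78.2%, 80.9%, 74.9% and 80.1%. About 80% is therefore fair at full response, although no single variant matches all four.

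**Step 2: allow for response.** For 16% v 30% at 70% response (83/180): s0 = 0.0579, s1 = 0.0528, and (0.14 − 1.96 × 0.0579)/0.0528 ≈ 0.503, so power is 69.2%. In full:

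| Response | non-LC / LC | 5 v 15% | 16 v 30% | 22 v 36% | 34 v 50% |
|---|---|---|---|---|---|
| 100% | 118 / 257 | 83.8% | 84.5% | 78.7% | 83.2% |
| 95% | 112 / 244 | 81.6% | 82.5% | 76.5% | 81.2% |
| 90% | 106 / 231 | 79.2% | 80.2% | 74.1% | 79.0% |
| 80% | 94 / 206 | 73.5% | 75.1% | 68.8% | 74.0% |
| 70% | 83 / 180 | 67.2% | 69.2% | 62.9% | 68.4% |

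The 95% row corresponds to losing refusals only.

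**Step 3: test the odds-ratio sentence at full response.** For odds ratio θ, p2 = θp1/(1 − p1 + θp1). At p1 = 0.16, θ = 2 gives p2 = 0.32/1.16 = 0.276, and θ = 0.5 gives p2 = 0.08/0.92 = 0.087. With 118/257:

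| Non-LC prevalence | Power, OR 2 | Power, OR 0.5 |
|---|---|---|
| 10% | 53% | 41% |
| 16% | 70% | 55% |
| 22% | 79% | 66% |
| 25% | 82% | 70% |
| 30% | 85% | 76% |
| 40% | 87% | 83% |
| 60% | 83% | 87% |
| 70% | 76% | 85% |

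On this calculation OR 2 has at least 80% power from about 25% to 60% prevalence, and OR 0.5 from about 35% to 70%. The appendix's own contrasts point the same way: 16% v 30% is an odds ratio of (0.30 × 0.84)/(0.16 × 0.70) = 2.25, so the effect listed as detectable at 16% is already larger than 2.

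All figures are unadjusted. Adjustment for age, sex, smoking and COPD, and patients without a known two-year outcome, are not allowed for.

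**The case against.** **The power statement is conditional and reproduces.** It says what 257 and 118 would give, and they do give roughly that. This stands: the defect is an unstated assumption of complete participation, and the calculation itself is sound.

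**The response figure is a lower bound from another population.** It is above 70%, from two centres in chest X-ray work. In IPCARD-SPN the questionnaire is given out before the scan visit and can be handed in there, which partly addresses the main cause of non-return. A reader might infer that true power is 63–69%. The documents do not support that as an expected value. It is the result at an assumed floor, and no response rate specific to IPCARD-SPN is given. What remains is that all four contrasts fall below 80% at 80% response, and three of the four do at 90%.

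**Rare symptoms are exempted, and the claim holds for many others.** The 10% row may fall within that exemption, and OR 2 at 22% misses by only one point. A reader might infer that the odds-ratio claim fails throughout. It does not; it is sound over the prevalence ranges given above. It fails as a statement about all non-rare symptoms, most clearly for odds ratios below 0.5, for which the appendix gives no power figure.

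**Main-trial precision.** A reader might extend the point to the confidence limits in Section 9.1, because "those without diagnosed lung cancer who drop-out before the end of 2 years will be excluded". The documents do not support that. The exclusion leaves diagnosed cancers in, Section 9.1 expects it to be small, and Section 5.4 obtains outcomes centrally for patients lost to follow-up. DCE-CT scans aborted under Section 5.3 take nothing from PET, and Section 7 counts patients who have undergone DCE-CT. No evaluable fraction is stated from which to recompute.

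**Conclusion.** The point holds for the IPCARD-SPN sub-study only. Its stated 80% power requires a questionnaire from every one of the 375 patients, which the protocol's own description of consent and past response does not support. Power for the four contrasts is 79–85% at full response, 74–80% at 90%, 69–75% at 80% and 63–69% at 70%. These figures rest on the pooled test, on equal response in patients with and without lung cancer, and on response rates that are assumed across a range.

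Independently of response, the odds-ratio sentence claims more than the design delivers. At 16% prevalence, power is 70% for OR 2 and 55% for OR 0.5. At 22% it is 79% and 66%, and at 30% OR 0.5 still has only 76%.

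The correction should be made, because a stated property of the design is not there and restating it is cheap. No main-trial objective or precision figure is affected.

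**What to change.** In Appendix 6, Sample Size:

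1. State that 257 and 118 assume complete participation, and give power for the four contrasts over a range of response rates (for example 70%, 80%, 90% and 100%, as tabulated above), naming the test used and saying that 70% is a floor taken from chest X-ray work.
2. Replace the odds-ratio sentence with the detectable odds ratio by symptom prevalence in patients without lung cancer, separately for odds ratios above and below 1.

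This costs wording only, and the stated figures become less favourable. Recruitment, procedures and analysis stay as they are, and Section 9.1 needs no change on this account.

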#### **RECRUITMENT STRATEGY AND CONSENT**

Potential SPUtNik participants will be introduced to the IPCARD-SPN study by the research nurse or PET coordinator either by phone or in clinic. They will be given the IPCARD-SPN questionnaire along with the SPUtNik patient information sheet, which contains a section about the IPCARD-SPN study.

The questionnaire contains no identifiable patient information. Patients may fill in the questionnaire prior to attending the scan appointments and bring it along to the scan appointment. At the scan appointment the research nurse or radiographer will take consent for the SPUtNik study, which includes an optional part for the IPCARD-SPN trial. If the patient consents to the IPCARD-SPN trial, the SPUtNik trial code will be added to the front of the questionnaire and completed questionnaires can be left with the research nurse. For incomplete questionnaires the SPUtNik code will be added and the patient given a Free-Post return envelope and asked to return the questionnaire by post within 2 days.

Participants will be told that they may withdraw consent at any time by telephoning the local hospital site a number is given on the patient information sheet.

Date received will be recorded for returned questionnaires and they will be prepared for automated data entry. Diagnosis will be obtained two years following recruitment from SPUtNik Trial data.

A second copy of the IPCARD questionnaire will be posted to all patients who have not received a lung cancer diagnosis after 1 year (12-18 months) of follow up. This copy will contain the SPUtNik code and be clearly marked IPCARD2. It will be posted with a cover letter explaining why the patient has been asked to complete the questionnaire for a second time and a prepaid envelope to return the questionnaire to SCTU.

Research staff, are instructed to ensure questionnaires are not sent to patients that have already received a diagnosis of lung cancer, are terminally ill or have died.

## DATA ANALYSIS

The predictive value of symptoms for lung cancer diagnosis will be identified at 12 (12 months from recruitment/questionnaire completion) and 24 months following questionnaire completion (end of study) for the first IPCARD questionnaire, and at 12 months following questionnaire completion (2 years from recruitment/ at end of study) for the second IPCARD questionnaire.

Logistic regression will be used to obtain unadjusted and adjusted odds ratios for symptoms. The models will be adjusted for age, sex and current smoking status and COPD status. COPD precedes lung cancer diagnosis in 40% to 90% of the cases and differences in prevalence of COPD between early stage and late stage lung cancer might explain differences in symptoms between these groups [14].

COPD will be defined by:

- Abnormal spirometry post-bronchodilator: defined as a forced expiratory volume in 1 second (FEV1) <70% of predicted and forced expiratory volume in 1 second/ forced vital capacity (FEV1: FVC) ratio <0.70. This is based on the American Thoracic Society standards agreed by most respiratory guidelines.

AND/OR

- Clinical diagnosis, by the chest clinic physician, based on the presence of symptoms such as recurrent cough (productive), wheezing, dyspnoea in conjunction with pre-disposing risk factors such as smoking, age and family history.

This data will be drawn from patients' medical records by research staff and will not be taken as part of the study

For the purposes of this study the implications of using a second definition of COPD (based upon evidence of emphysema identified by CT scan) will also be explored. It is possible that early symptoms experienced by those with resectable lung cancer might be explained by emphysema.

Age, sex and further common comorbidities which are found to differ between the LC and non-LC populations, and share symptoms with lung cancer will be included as covariates in the multivariate models. Previous research has found interactions between symptoms and risk factors to have higher PPVs than symptoms alone [6]. Items to identify individual risk of LC were included in IPCARD to determine the interaction of symptoms and established epidemiological risk factors [13], further refining estimates of individual risk in those with symptoms. Clinically plausible interactions between symptoms and interactions between symptoms and risk factors/comorbidities (pack years smoked, family history of cancer, previous malignancy, previous pneumonia, asthma, and acute respiratory infections) will be tested in the final model.

Multivariable analyses –developing a model to predict lung cancer diagnosis: A multivariable model will be developed which will be adjusted for age, sex, current smoking status, COPD status and common comorbidities where these differ between lung cancer and non-lung cancer. Clinically plausible interactions between symptoms, and interactions between symptoms and risk factors/comorbidities (pack years smoked, family history of cancer, previous malignancy, previous pneumonia, asthma, and acute respiratory infections)

will be tested. All symptoms with an association with LC in univariate analyses will be entered into the final model.

Modelling strategy: Univariate logistic regression will be used to explore associations between each of the symptoms and the outcome variable (lung cancer). Forward stepwise multiple logistic regression analysis will be used to enter symptom variables into the analysis which were associated with lung cancer in univariate analysis ( $p < 0.05$ ). The criteria for entry into the model will be  $p \leq 0.05$  and criteria for removal will be  $p \geq 0.1$ . To reassess variables discarded through the stepwise process, each in turn will be added to the final model and any improvement in predictive value ( $R^2$ ) noted. The adjusted odds ratios for symptoms will be reported with  $p$  values. Symptoms with an independent relationship with LC will be included in a simple score (each symptom variable is given a value of 1). Analyses will calculate the sensitivity, specificity and predictive values for various levels of cut-offs to determine the optimal threshold at which the score best distinguishes between those with and without lung cancer.

